#### Secondary outcomes

Secondary outcomes will include: 7 day point prevalence abstinence (via bot) at 1 and 3 months; change in cigarettes per day; change in Fagerström test for nicotine dependence (FTND) score; change in Prochaska’s Motivation to Quit Smoking Questionnaire score (0–8); engagement metrics (weekly check-in completion rate, SOS-button presses); intervention acceptability/satisfaction score (12-item Likert scale); and time to first relapse (any cigarette) after ≥24 h of abstinence. Data collection, time points, mode of assessment, and the questionnaires administered are summarized in Table 1. Missing data will be reported and accounted for in the analysis (for secondary outcomes based on available cases).

**Table 1 T1:** Schedule of outcomes and assessments in the TELEGRAM-MI pragmatic randomized trial testing a Telegram-based intervention for smoking cessation after myocardial infarction, Russia, 2026

Outcome	Type	Measurement tool/ source	Baseline	1 **month**	3 **months**	6 **months**
30 day point prevalence abstinence	Primary	Blinded phone interview + relative confirmation				X
7 day point prevalence abstinence	Secondary	Telegram bot self-report		X	X	X
Cigarettes per day	Secondary	Telegram bot self-report	X	X	X	X
FTND score	Secondary	Fagerström test for nicotine dependence (bot)	X			X
Motivation to quit^a^	Secondary	Self-rated scale via Telegram bot	X			X
Engagement metrics^b^	Secondary	Automatically logged by Telegram bot		X	X	X
Acceptability/ satisfaction score	Secondary	Custom questionnaire via Telegram bot (intervention only)				X
Time to first relapse	Secondary	Continuous monitoring via weekly check-ins (bot)		X	X	X

a Prochaska questionnaire (0–6).

b Check-ins, openings etc.

FTND: Fagerström test for nicotine dependence.

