### Interventions

#### Control group (usual care + passive bot)

Participants receive usual care (advice to quit and pharmacotherapy at the discretion of the physician) and are connected to a Telegram bot used only for completing baseline and follow-up assessments (1, 3, and 6 months). The control bot sends no smoking-cessation advice, motivational content, or personalized feedback.

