#### Intervention group (usual care + active telegram support)

Participants received a 6 month behavioral intervention via a Telegram chatbot. The bot delivered content across several categories (e.g. motivational^9^, behavioral coping strategies^10^, check-in prompts) following a tapered frequency schedule: daily messages during months 1–2, reducing to three times per week in months 3–4, and weekly in months 5–6. Personalization was rule-based: initial intensity was informed by the baseline Fagerström score, and subsequent support was dynamically adapted based on weekly check-in responses (e.g. increased outreach following reports of high cravings or lapse). Bot script will be shared.

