### Statistical analysis

Analyses will follow the intention-to-treat principle, with participants lost to follow-up considered smokers for the primary outcome. Baseline characteristics will be presented descriptively in Table 2^6^. The primary analysis will compare 6 month abstinence rates using a chi-squared test, reporting absolute risk difference and relative risk (RR) with 95% confidence intervals (CIs). Continuous outcomes will be analyzed using linear mixed models. Time to first relapse will be analyzed with Kaplan-Meier curves and Cox regression. Exploratory analyses will use logistic regression to assess associations between baseline factors, engagement, and cessation. A per-protocol secondary analysis will include intervention-group participants who completed ≥60% of weekly check-ins during the first 3 months and had their final assessment within 6 months±3 weeks; this criterion does not apply to the control group.

**Table 2 T2:** Baseline demographic and clinical characteristics of TELEGRAM-MI participants by trial arm (template for future Table)

Characteristics	Total	Intervention	Control

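### Time to first relapse is sourced from weekly check-ins that the control bot does not carry, so the planned Kaplan-Meier and Cox comparison has no stated common measurement in the two arms

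*Protocol article*

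**What the plan says.** All references are to the protocol article.

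- **Secondary outcomes** defines the event as "time to first relapse (any cigarette) after ≥24 h of abstinence".
- **Table 1** gives its source as "Continuous monitoring via weekly check-ins (bot", with marks at months 1, 3 and 6 and no restriction by arm. The acceptability row just above is restricted: "Custom questionnaire via Telegram bot (intervention only".
- **Control group** says these participants "are connected to a Telegram bot used only for completing baseline and follow-up assessments (1, 3, and 6 months".
- **Intervention group** makes the weekly check-in part of the treatment: "subsequent support was dynamically adapted based on weekly check-in responses".
- **Statistical analysis** sets a per-protocol rule based on check-in completion and adds that "this criterion does not apply to the control group". The same section states: "Time to first relapse will be analyzed with Kaplan-Meier curves and Cox regression". It says nothing about contact schedules that differ by arm.

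**The concern.** The instrument named for this outcome cannot produce data for control participants if the control bot works as described. A survival comparison needs the event to be detected in the same way in both groups. If one arm is asked every week and the other after roughly one, three and six months, the curves can separate because of the questioning alone.

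The other bot measures listed for controls during follow-up do not fill the gap. Seven-day abstinence and cigarettes per day do not ask when the first cigarette was smoked, and a seven-day window can miss a lapse between visits although a single cigarette counts as an event.

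At stake is the hazard ratio for one secondary outcome. It could show a difference where none exists, or blur a real one.

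**Working it through.** **1. The plan's own figures.** The plan gives no figure for time to relapse. Its sample size is used below only as the number per arm: 60 / (1 − 0.15) = 70.6, rounded up to 71, as stated. The underlying 60 per group for 10% versus 30% lies between the unpooled formula (59) and the pooled formula (62).

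**2. The sections side by side.** Table 1 makes weekly check-ins the source for a row that covers the whole trial. The control-group section allows contacts only at baseline and months 1, 3 and 6. Both cannot hold for a control participant.

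**3. A hand calculation of the mechanism.** Inputs assumed, because the article gives no relapse-time distribution: the same constant relapse hazard in both arms, 30% relapse-free at day 182, and each relapse dated at the next contact. Contacts are weekly in the active arm and at days 30, 91 and 182 in control. The proportion relapsed by day t is 1 − 0.30^(t/182).

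- Recorded by day 90, active arm (last contact day 84): 1 − 0.30^(84/182) = 1 − 0.574 = 42.6%.
- Recorded by day 90, control arm (last contact day 30): 1 − 0.30^(30/182) = 1 − 0.820 = 18.0%.
- Recorded by day 182: 70% in both arms.

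The true curves are identical, yet the recorded curves are far apart at day 90 and meet again at the end.

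**4. Effect on the Cox model, no true difference.** Simulation with 71 per arm, 182 days, Weibull relapse times (shape 1.0 and 0.6), Efron ties, 600 trials per scenario and the dating rule of step 3. The 50% and 85% rows come from a repeat run on the same dating assumption; the 70% and 90% rows span both runs. A ratio above 1 means that the active arm appears to relapse sooner.

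| Relapsed by 6 months (assumed) | Hazard ratio, active vs control | Rejection at nominal 5% |
|---|---|---|
| 50% | about 1.13 | 8–10% |
| 70% | 1.19–1.22 | 13–17% |
| 80% | 1.28–1.30 | 24–28% |
| 85% | 1.32–1.36 | 33–40% |
| 90% | 1.40–1.44 | 44–53% |

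**5. The same null case under other assumptions.**

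- Controls recall the exact date at each visit: ratio 0.92–1.01, rejection 3–8%.
- Control relapse dated at the next contact, but 30% of relapsing active participants stop checking in and are censored (70–90% relapse): ratio 0.85–1.04, rejection 6.5–11%.
- Same grid in both arms, weekly or at the three visits: ratio 0.99–1.01, rejection 2.5–5.8%.

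**6. With a true difference.** Take 30% versus 10% relapse-free at six months. These borrow the plan's abstinence rates, which are not the same quantity, so this too is an assumption. The true ratio is ln 0.30 / ln 0.10 = 1.204 / 2.303 = 0.52.

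| Ascertainment | Hazard ratio | Power |
|---|---|---|
| Exact dates | 0.52 | 93% |
| Weekly vs visits | 0.67–0.68 | about 56% |
| Weekly vs visits, 30% drop-out at relapse | 0.47–0.48 | 93–94% |
| Visits in both arms | 0.53 | 92% |

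Unequal grids can hide the effect, and drop-out can make it look slightly larger than it is. A coarse common grid costs almost nothing.

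**The case against.** The strongest reply is that the article never says how control relapse is dated. It gives the times of contact, not the questions asked, and the bot script is not shown. Three readings fit: relapse is dated at the visit, controls are asked for the date of the first cigarette, or the outcome exists only in the active arm. The statistical section names the methods without naming a between-arm contrast. The missing arm restriction does not settle the matter, because the engagement row includes check-ins and is also unrestricted, so Table 1 does not label arms consistently. All of this stands. It makes the figures in steps 3 and 4 conditional, but it does not remove the contradiction between the stated sections. A later analysis plan could not recover dates that were never asked for.

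A reader might go further and infer that control relapses are known to be recorded at months 1, 3 and 6, so that the comparison is biased against the active arm. The document does not support this. Dating at visits is an inference, accurate recall removes most of the distortion, and drop-out from check-ins works in the opposite direction.

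A reader might also object that the 24-hour condition selects participants on an event after randomisation. The text gives little ground for this. Enrolment and connection to the bot take place during the hospital stay, and the Discussion describes enforced withdrawal there, so many participants may meet the condition at or before randomisation. The point made here does not rely on it.

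**Conclusion.** The inconsistency is real and should be fixed. As written, time to first relapse has a described source in the active arm and none in the control arm, so a between-arm Kaplan-Meier or Cox result would compare different ascertainment.

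The size depends on what controls are asked. Dating at the next contact would give a spurious hazard ratio of about 1.13 to 1.4 for 50% to 90% relapse, with false-positive rates from about 8–10% to about 50%. Exact recall would leave the ratio near 1. Drop-out at relapse could take it below 1. The relapse proportions, the Weibull shapes and the 30% drop-out are all assumptions, and neither the direction nor the size of the net bias can be fixed from the document.

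It would be too strong to call this a flaw in the trial as a whole. It concerns one secondary outcome that carries no sample size of its own. The primary outcome, its chi-squared test and the target of 142 are untouched.

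**What to change.** 1. Reconcile the Table 1 row with the control-group section, and state the source of relapse data for each arm.
2. At months 1, 3 and 6, ask both arms the same question: any cigarette since discharge and, if so, the date of the first.
3. Base the between-arm comparison on that common source, with a discrete-time or interval-censored model on the 0–1, 1–3 and 3–6 month intervals. The date helps to place an event in the right interval when a visit was missed.
4. Use the weekly check-in dates only descriptively, within the active arm.

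The cost is one extra item in surveys that both bots already deliver, a change of analysis wording, and coarser relapse timing in the active arm. In step 6 of the working, that coarsening moved power only from 93% to 92%. The item needs to be in place before the first month-1 assessments, since a date not asked for then has to be recalled later. The change does not prevent non-response after relapse, but it puts both arms on the same schedule, so that missing answers can be compared between them.

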### Sample size calculation

Assuming 6 month abstinence rates of 10% (control)^4^ and 30% (intervention), 120 participants (60/group) are needed for 80% power with a two-sided alpha of 0.05. Allowing for a 15% dropout rate, the target sample size is 142 (71/group). The assumptions are based on prior evidence, where abstinence after brief advice is around 10%^9^, and a larger effect is considered plausible due to the acute motivational impact of myocardial infarction^11^.

### Statistical analysis

Analyses will follow the intention-to-treat principle, with participants lost to follow-up considered smokers for the primary outcome. Baseline characteristics will be presented descriptively in Table 2^6^. The primary analysis will compare 6 month abstinence rates using a chi-squared test, reporting absolute risk difference and relative risk (RR) with 95% confidence intervals (CIs). Continuous outcomes will be analyzed using linear mixed models. Time to first relapse will be analyzed with Kaplan-Meier curves and Cox regression. Exploratory analyses will use logistic regression to assess associations between baseline factors, engagement, and cessation. A per-protocol secondary analysis will include intervention-group participants who completed ≥60% of weekly check-ins during the first 3 months and had their final assessment within 6 months±3 weeks; this criterion does not apply to the control group.

**Table 2 T2:** Baseline demographic and clinical characteristics of TELEGRAM-MI participants by trial arm (template for future Table)

Characteristics	Total	Intervention	Control

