### Recruitment, consent, and randomization

A treating cardiologist or study nurse will screen potential participants. After providing written informed consent, participants will be assisted in connecting to the study’s Telegram bot before discharge. Randomization will occur automatically within the bot upon completion of the baseline assessment. The allocation sequence (1 : 1) will be computer-generated with variable block sizes by an independent statistician using R software and integrated into the bot’s backend. Allocation concealment is ensured, as the enrolling clinician will have no access to the sequence; the group assignment is revealed only by the bot after the baseline survey is finalized. The flow of participants through the study is illustrated in Figure 1.

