**Smoking-related**			
Cigarettes per day, mean (SD)			
Years of smoking, mean (SD)			
FTND score (0–10), mean (SD)			
FTND≥6 (high dependence), n (%)			
Previous quit attempts (past year), n (%)			
Motivation to quit^a^, mean (SD)			

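### The primary chi-squared test is valid but leaves unused the baseline smoking measures taken on everyone before randomisation, at a modest cost in precision

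*Protocol article*

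**What the plan says.** Protocol article, Statistical analysis: "The primary analysis will compare 6 month abstinence rates using a chi-squared test", with the risk difference and relative risk given with 95% confidence intervals. Participants lost to follow-up count as smokers, so all randomised participants are analysed. Baseline factors enter a model for abstinence only in an exploratory logistic regression of associations, not in the treatment comparison.

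Recruitment, consent, and randomization: "The allocation sequence (1 : 1) will be computer-generated with variable block sizes by an independent statistician". No stratification factor is named. The bot allocates only once the baseline assessment is complete.

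Table 1 schedules cigarettes per day, FTND and motivation to quit at baseline, and the Table 2 template lists all three.

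Sample size calculation: with 10% abstinent under control and "30% (intervention), 120 participants (60/group) are needed" for "80% power with a two-sided alpha of 0.05". A 15% dropout allowance then gives 142 (71 per group).

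**The concern.** In a trial of 142 patients with few expected abstainers, baseline measures that predict quitting can sharpen the treatment comparison. Here they are already collected and should be complete, because allocation waits for them. The design does not balance the arms on them and the primary analysis does not use them.

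At stake is some power, together with protection of the single reported estimate against chance imbalance. As an illustration, suppose 40% of participants have FTND of 6 or more (assumption). The between-arm difference then has standard error √(2 × 0.40 × 0.60 / 71) = 8.2 percentage points, so an imbalance of 10 points or more would occur in about 22% of trials of this size. A covariate chosen after the data are seen would not be a credible answer to such an imbalance. The choice has to be made in advance.

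**Working it through.** **1. The plan's own figure.** Inputs from Sample size calculation: 10% vs 30%, two-sided alpha 0.05, 80% power.
- Unpooled formula: n = (1.960 + 0.842)² × (0.10 × 0.90 + 0.30 × 0.70) / 0.20² = 58.9 per group.
- Arcsine formula: 59.0. Pooled formula: 62.
- Dropout: 120 / 0.85 = 141.2, rounded up to 142.

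The stated 60 and 71 per group therefore reproduce for an unadjusted comparison. The design does not rely on adjustment.

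**2. Unadjusted power at 71 per arm.** Power = Φ{[d√n − 1.96√(2p̄(1 − p̄))] / √(p₀(1 − p₀) + p₁(1 − p₁))}, where d = p₁ − p₀ and p̄ is the mean of the two rates. The article does not say whether 10% and 30% already count dropouts as smokers, so both readings are shown.
- Reading A, they do (10% vs 30%): [0.20 × 8.426 − 1.96 × 0.5657] / 0.5477 = 1.053, power 85.4%. Expected abstainers: 71 × 0.40 = 28.
- Reading B, they apply to completers and 15% are lost. The rates become 0.85 × 10% = 8.5% and 0.85 × 30% = 25.5%: [0.17 × 8.426 − 1.96 × 0.5312] / 0.5174 = 0.756, power 77.5% (79.1% unpooled, 79.5% arcsine). Expected abstainers: 71 × 0.34 = 24.

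**3. Effect of adjustment, by formula.** If the covariates explain a fraction R² of outcome variance, the effective n is about 71 / (1 − R²). R² is an assumption; the document gives no value.

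| R² | Reading A | Reading B |
|---|---|---|
| 0% | 85.4% | 77.5% |
| 2% | 86.1% | 78.4% |
| 5% | 87.1% | 79.6% |
| 10% | 88.9% | 81.8% |
| 15% | 90.5% | 83.9% |

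**4. Simulation.** 5,000 trials per scenario, 71 per arm, 10% vs 30%, three covariates. AUC is the combined discrimination of the covariates (assumed).

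| AUC | Chi-squared | Adjusted logistic |
|---|---|---|
| 0.50 (useless) | 86.9% | 86.5% |
| 0.60 | 87.3% | 87.3% |
| 0.66 | 87.5% | 88.9% |
| 0.73 | 87.1% | 90.5% |
| 0.79 | 87.0% | 92.1% |

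Standardised risk differences gave nearly the same power as the adjusted logistic test. With a smaller true effect (10% vs 25%, assumed), chi-squared power is about 67% and the gains over the last four rows are about 1.4, 2.3, 4.7 and 8.2 points.

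With two covariates and a robust small-sample variance, the gain was about 0 to 4 points under Reading A and 0 to 6 under Reading B. Useless covariates cost essentially nothing.

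**5. Type I error.** With 10% in both arms (71 × 0.20 = about 14 abstainers) and three covariates, rejection rates were 4.7–5.4% for chi-squared, 5.3–6.2% for the adjusted logistic test and 5.0–5.9% for standardisation. With two covariates and the small-sample variance, standardisation ran at 4.5–5.6% against 4.4–5.1% for chi-squared. The simulation standard error is √(0.05 × 0.95 / 5000) = 0.3 points.

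**The case against.** The strongest reply is that nothing here is wrong. A chi-squared test is valid under 1:1 blocked randomisation, it matches the comparison that was powered, and no stratification factor is being ignored because none was used. All of that stands. An adjusted supporting analysis may also sit in a statistical analysis plan that is not shown, so its absence from the article is not held against the trial. The article does, however, fix the primary test itself.

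Three stronger readings are tempting, and the document supports none of them.

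- **The covariates are strongly prognostic.** No figure is given. The article uses FTND to set initial message intensity and plans to relate baseline factors to cessation, which makes prognostic value plausible and no more. The Discussion even says that cessation in this group often stems from the medical crisis and not from personal readiness, which weakens the case for motivation.
- **The trial is underpowered without adjustment.** That follows only under Reading B, where power is about 78–80%. Under Reading A it is about 85%, above target.
- **Unstratified randomisation biases the result.** Chance imbalance is not bias. It does not inflate the type I error, and the unadjusted interval already allows for it.

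It is also fair to say that part of the simulated gain with three covariates may be slight size inflation. That argues for fewer covariates and a careful variance estimate.

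**Conclusion.** The point holds as a missed gain in precision. Under the assumed range of covariate strength, from none to moderate, adjustment adds about 0 to 5 points to about 85% power if 10% and 30% already score dropouts as smokers, and about 0 to 6 points to about 78–80% if they do not. With weak covariates the gain is nil. If the true effect is smaller than planned it could reach about 8 points, with three covariates at the top of the assumed range.

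The facts behind the point are certain: an unadjusted primary test, baseline measures taken before allocation, and no stratification named. The size of the gain is not. A change is worth making because it is cheap and keeps the estimand, not because the present test is faulty.

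**What to change.** Before any outcome data are seen:

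- Make the primary analysis a logistic model with arm and at most two continuous baseline covariates, FTND and cigarettes per day.
- From it, report the marginal risk difference and relative risk by standardisation (g-computation), so that the target stays what the article already reports. Give 95% intervals from a robust, small-sample-corrected variance or the bootstrap.
- Keep the chi-squared test as the supportive unadjusted analysis.
- Use motivation to quit as a covariate only once its range is reconciled: the Secondary outcomes text gives 0–8, while the footnotes to Tables 1 and 2 give 0–6.
- State in the sample-size section whether 10% and 30% already count dropouts as smokers.

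The cost is protocol and analysis-plan wording plus standard software, with no new data or visits. The drawbacks are a slightly more complex analysis with about 24 to 28 events and a possible minor rise in type I error (about 5.5% in simulation). The variance method should therefore be checked at this sample size before it is fixed.

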### Outcomes and assessments

#### Primary outcome

The primary outcome will be 30 day point prevalence abstinence (PPA) at 6 months, defined as self-reported non-smoking via bot for the preceding 30 days corroborated by a relative/cohabitant report during a blinded telephone interview. Participants with missing data or data not corroborated by a relative after two attempts will be considered smoking.

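### Time to first relapse: analysing available cases with Kaplan-Meier and Cox would ordinarily censor silent participants, which is biased if silence marks relapse, as the primary outcome rule presumes

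*Protocol article*

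**What the plan says.** All references are to the protocol article.

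- Secondary outcomes defines the event as "time to first relapse (any cigarette) after ≥24 h of abstinence". Table 1 gives weekly bot check-ins as its source and does not limit them to one arm.
- Statistical analysis: "Time to first relapse will be analyzed with Kaplan-Meier curves and Cox regression".
- Secondary outcomes, on missing data: handled "for secondary outcomes based on available cases".
- Primary outcome: "Participants with missing data or data not corroborated by a relative after two attempts will be considered smoking". Statistical analysis repeats this, "with participants lost to follow-up considered smokers for the primary outcome", and so confines it to that outcome.
- Control group: the control bot is used only for the baseline assessment and the 1-, 3- and 6-month assessments, so that section gives controls no weekly contact.
- Sample size calculation: 10% v 30% abstinent at 6 months, with 15% dropout.

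The article does not say when a participant who stops answering leaves the time-to-relapse analysis.

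**The concern.** A relapse enters this analysis only if the participant reports it to the bot. Under an available-case rule, someone who stops answering without reporting a relapse contributes time up to the last answer and is then censored. Kaplan-Meier and Cox assume that such a person has the same later relapse risk as those who keep answering. A participant who stops answering because of a relapse breaks that assumption, and neither method corrects for it.

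The primary outcome takes the opposite view of non-response. A participant who falls silent and never supplies the 6-month outcome would be a smoker in the primary analysis and a censored non-event in this one. Two things are at stake. The relapse-free curve would be too high in any arm with silent relapsers, and the hazard ratio would partly reflect which arm goes silent more often. Equal silence cannot be taken for granted, because the two bots contact participants on different schedules and with different content.

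**Working it through.** **The plan's own figure.** No number is stated for time to first relapse. The only planning input used here is the 15% dropout, and its use in the plan reproduces: 120/(1 − 0.15) = 141.2, rounded up to 142.

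**Inputs.** From the plan: dropout d = 0.15 and 6-month abstinence of 10% and 30%. Assumptions not in the documents:
- those two rates stand in for the relapse-free share S at 26 weeks;
- the hazard is constant;
- both arms are observed on the same weekly grid;
- every silent participant fell silent at relapse;
- the by-arm silence rates are as shown below.

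**Effect on the curve.** The share of relapsers who are silent is q = d/(1 − S). Censoring them scales the observed hazard by 1 − q, so the estimated relapse-free share is S^(1 − q).

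| True S | q at d = 0.15 | 1 − q | Estimated share |
|---|---|---|---|
| 0.10 | 0.15/0.90 = 0.167 | 0.833 | 0.10^0.833 = 0.147 |
| 0.20 | 0.15/0.80 = 0.188 | 0.813 | 0.20^0.813 = 0.270 |
| 0.30 | 0.15/0.70 = 0.214 | 0.786 | 0.30^0.786 = 0.388 |
| 0.40 | 0.15/0.60 = 0.250 | 0.750 | 0.40^0.750 = 0.503 |

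A weekly-grid simulation with 6,000 per arm agrees. With 15% silent, realised shares of 9.7% and 28.8% were estimated as 14.0% and 37.5%.

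**Hazard ratio with no true effect.** The estimate is the ratio of the two values of 1 − q. With 10% silent in control and 20% in intervention:
- S = 0.30 in both arms: (1 − 0.20/0.70)/(1 − 0.10/0.70) = 0.714/0.857 = 0.83; with the arms reversed, 1.20.
- S = 0.10 in both arms: (1 − 0.20/0.90)/(1 − 0.10/0.90) = 0.778/0.889 = 0.875; with the arms reversed, 1.14.

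In the simulation at S = 0.10, the figures were 0.88 and 1.11. With equal silence of 15%, the hazard ratio stayed at 1.0.

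**Hazard ratio with the planned effect.** The true value is ln 0.30/ln 0.10 = 1.204/2.303 = 0.52.
- 15% silent in each arm: 0.523 × 0.786/0.833 = 0.49.
- 10% control, 20% intervention: 0.523 × 0.714/0.889 = 0.42.
- 20% control, 10% intervention: 0.523 × 0.857/0.778 = 0.58.

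The simulation gave 0.51, 0.43 and 0.59, against realised true values of 0.53 to 0.55.

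**If silence is independent of relapse.** Censoring at 15% returned 9.7% and 29.7%, against realised values of 9.7% and 29.8%, with a hazard ratio of 0.54 either way. Counting silence as relapse is then the biased choice. It multiplies S by 0.85, giving 0.085 and 0.255 (simulation 8% and 26%).

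**The case against.** Several stronger readings are tempting, and the documents do not support them.

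- **That the plan counts silent participants as relapse-free.** A censored participant leaves the risk set and is assumed to share the later risk of those who remain. The censoring itself is inferred from the available-case rule. The detailed rule may sit in an analysis plan that is not shown.
- **That relapse-free survival is overstated as a matter of fact.** This needs a link between silence and relapse. Missing-equals-smoking can be a conservative convention for a binary endpoint without being a claim about why people stop replying.
- **That the two analyses must contradict each other in the same people.** A participant who skips check-ins but answers at 6 months, with a relative's corroboration, is not scored as smoking.
- **That a spurious hazard ratio of a known size follows.** No by-arm silence rate is given, and with equal silence and no effect there is no shift. With about 71 × (0.90 + 0.70) = 114 relapses, the 95% interval spans a factor of about exp(1.96 × 2/√114) = 1.44 either way, so a shift to 0.83 lies within sampling error.
- **That counting silence as relapse is simply the better main analysis.** It is biased if silence is independent of relapse. It also depends on the contact schedule. If controls are contacted only at 1, 3 and 6 months and the other arm weekly, the first unanswered contact comes much sooner in the intervention arm. A simulation on those schedules with no effect and 10% v 20% relapse-linked silence gave hazard ratios of about 1.23 and 1.39 (30% and 10% relapse-free), against 0.98 and 1.19 with censoring.

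All of these limits stand. What they leave is that the article does fix a missing-data rule for this outcome, and that the rule rests on the reverse of the assumption made for the primary outcome.

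**Conclusion.** The point holds conditionally. If silence marks relapse, censoring at the last answer is informative. At the plan's 15% dropout it raises a true 30% to about 39% and a true 10% to about 15%. An assumed 10% v 20% split in silence moves a null hazard ratio to about 0.83 to 0.88, or 1.14 to 1.20 with the arms reversed. These figures rest on a constant hazard, a common weekly grid and every silent participant having relapsed, so they are the upper end of the effect for those silence rates. If silence is unrelated to relapse, the bias is nil. The documents cannot settle which case applies, so one analysis under either assumption leaves the result exposed. This is a minor-to-moderate point on one secondary outcome, and the primary analysis is unaffected.

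**What to change.** State the censoring rule for time to first relapse and pre-specify two analyses:

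1. participants who stop responding without a reported relapse are censored at their last answer;
2. the same participants are counted as relapsed at the first unanswered assessment.

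Both should use assessment times common to the two arms. On the control-group section as written, these are 1, 3 and 6 months. That section and the weekly check-ins in Table 1 must be reconciled first. Interpret the hazard ratio only where the two analyses agree.

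The cost is a sentence or two of wording and one extra model run. Event times become coarser, because the weekly detail in the intervention arm is not used for the comparison. In the second analysis, some true abstainers who merely stop replying are counted as relapsed.
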